### Materials and procedures

Through the conduct of our previous study (iQuaD) we have developed and tested many of the instruments and data collection methods that will be used in the trial described in this protocol. The study outcome measures will be the proportion of patients recorded or reporting appropriately receiving each of the six study behaviours. We have successfully measured these behaviours in our previous study [9].

### Outcome measures (patient survey)

We will use a short questionnaire to assess patients’ reports of having received care, assessed 12 months after the intervention delivery. The three advising behaviours are not reliably recorded in general practice computer systems [9], and measures of these will be acquired by a self-administered patient survey.

Using an anonymous survey we will ask people with diabetes in the study practices about their experiences of their clinicians providing advice about nutrition, physical activity, general education about their diabetes and foot examination, and their confidence in understanding and enacting of their diabetes care.

Each practice will be provided with 100 patient questionnaires, coded by the research team with their practice study code and a patient code of 1 – 100 (*e.g.* 001/001), and 100 reply paid envelopes. Patients will return their questionnaires directly to the research team. The practice will not be aware of which patients have or have not responded to the questionnaire, giving further protection to patients’ confidentiality.

We will explore the potential of conducting a second mailing to the same random sample of patients a month later to promote a higher response. Patient consent to participate in the anonymised survey will be assumed by the receipt of a completed questionnaire.

### Outcome measures (computer read codes from patient electronic records)

#### Prescribing behaviours and foot examination

The behaviours relating to prescribing (prescribing additional antihypertensive drugs, prescribing additional therapy for managing glycaemic control) and foot examination are measured by extracting clinical and prescribing data from general practice computers using electronic queries developed and used in our previous study. We will study both the performance of clinical behaviours (measuring HbA1c, BP, foot checks) and the associated biochemical/physiological measurement (level of HbA1c; level of BP), accepting that there will be variability in the latter measures reflecting patient physiology and health behaviour. The data will relate to the 12-month period following intervention delivery and be extracted after month 12. Data will be extracted for a 24-month period (*i.e.*, 12 months prior to and 12 months after the month within which the intervention is delivered). We will thus account for any seasonal effects in performance of the target behaviours. The search queries will be sent to each practice, with written guidelines for how to run the query. For all registered patients with diabetes the research nurses will run computer queries to extract data on the total number of patients with diabetes in the practice and the number who have had: a foot check; blood pressure, HbA1c, and weight measured; level of systolic and diastolic blood pressure, level of HbA1c, cholesterol and body mass index; and diabetes-related medication (hypoglycaemic drugs, weight reducing drugs). We will pilot the data extraction procedure with an experienced NHS performance data manager to ensure reliability in data extraction.

#### Quality and outcomes framework data

The QOF is a voluntary annual reward and incentive programme for all primary care practices in the UK. The QOF details practice-level performance on a number of key indicators across organisational and clinical areas including diabetes. The data are publicly available from the NHS Information Centre http://www.ic.nhs.uk/. The QOF data for diabetes mellitus and practice organisation will be collected for each participating practice for the 12-month period of QOF data collection best matching the 12-month period before and again after baseline questionnaire completion.

### Process measures (clinician questionnaire)

We will post a baseline questionnaire prior to delivery of the intervention and a 12-month follow-up questionnaire to each identified practice contact for distribution to clinicians identified as involved in providing care to people with type 2 diabetes along with a postage paid return envelope. Two reminders will also be sent at baseline and follow-up to non-respondents to promote a higher response.

### Analysis

#### Main trial analysis

Practice attributes will be described. The primary analysis will involve testing, for each behaviour, whether there is a difference between intervention and control in the proportion of patients in each practice for whom the behaviour was undertaken during the 12 months following the intervention delivery. Rates of behaviour in intervention and control practices will be compared using a multilevel regression model taking into account the clustering of patients within practices. Practice list size will be included as a covariate given its use as a stratification factor. We will also consider specialist diabetes clinic and onsite insulin prescription as covariates depending on bivariate correlations. For the two prescribing behaviours the rates at which patients received the behaviour prior to the intervention will also be included as covariates in the analysis. The main analysis will be ‘intention to treat’; practices randomised to receive the intervention will be compared with other practices. A secondary ‘as treated’ analysis will take into account the uptake of the intervention in each practice.

In the case that outcome is missing for individual patients if we have other relevant variables for those individuals we will impute missing values using the ‘across cluster random-effects logistic regression method’ described by Ma *et al.*[42]. In the case of missing clusters no imputation will be undertaken. The potential impact of missing clusters on the estimated impact of the intervention will be assessed using sensitivity analysis involving a range of assumptions about the performance of the missing clusters.

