**5.** Over the past 12 months **prescribe additional antihypertensive** drugs for patients with type 2 diabetes whose blood pressure is 5 mmHg above target of 140 mmHg (systolic) or 80 mmHg (diastolic) even following previous management	Received by 40% whose blood pressure (BP) is above a target of 140 mm Hg for Systolic BP or 80 mm Hg for Diastolic BP, even following previous management (via practice-held prescribing data)	QS5 - ‘People with diabetes agree with their healthcare professional to start, review and stop medications to lower blood glucose, blood pressure and blood lipids in accordance with NICE guidance’
**6.** Over the past 12 months **examined foot** circulation and sensation in the feet of patients with type 2 diabetes	Received by 91% of patients (via patient survey)	QS10 - ‘People with diabetes at risk of foot ulceration receive regular review by a foot protection team in accordance with NICE guidance’
		QS11 - ‘People with diabetes with a foot problem requiring urgent medical attention are referred to and treated by a multidisciplinary foot care team within 24 hours’

^a^From NICE quality standard for diabetes in adults (http://www.nice.org.uk/media/7F8/B2/DiabetesQualityStandard.pdf).

Note. QOF = Quality and Outcomes Framework.

Our results showed that in primary care, individual healthcare professionals’ beliefs about these behaviours predicted their clinical behaviour while their perceptions about their workplace did not; multilevel models also showed that variability was primarily between individual clinicians within general practices rather than between the practices [10]. Based on these findings, an intervention targeting individuals within organisations rather than targeting their organisation may be more likely to be effective.

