#### Step three: patient recruitment

From our previous study [9], we identified that advising behaviours are not consistently recorded in patient notes. We therefore conducted a patient survey to ask patients to report on whether they had received this care in the past year. Consistent with this approach, we will invite a random sample of 100 patients with type 2 diabetes from each practice to complete an anonymous postal questionnaire 12 months after the delivery of the intervention. Patients with type 2 diabetes will be randomly selected from practice lists by the study contact in each recruited practice using a random sequence provided by the study statistician. Patients will be anonymous to the research team.

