### Primary outcomes

The primary outcomes will be based on behaviours as measured in our previous study, updated to be consistent with NICE Quality Standards for Type 2 diabetes. Updates include necessary minor modifications to the thresholds (compared to those used in our previous study) in the two prescribing behaviours (for HbA1c and blood pressure control) in light of evolving guidance, and the advising behaviours in light of the specific wording of the NICE Quality Standards. We will also explore the capacity to use QOF data as secondary sources of data, depending on the available indicators at the time of follow-up. Table 2 describes the primary outcomes, and the primary and secondary sources of data.

**Table 2 T2:** Primary outcome measures and data sources

**Outcome (clinical behaviours)**	**Primary data source**	**Secondary data sources**
**1.****Provide personalised nutrition advice** to patients with type 2 diabetes whose BMI is above a target of 30 kg/m^2^ even following previous management	Patient survey @ 12 months (receipt of advice)	Clinician survey @ 12 months; QOF
**2.****Provide on-going education** about diabetes for patients with type 2 diabetes	Patient survey @ 12 months (receipt of education)	Clinician survey @ 12 months; QOF
**3.****Provide personalised advice on physical activity** for patients with type 2 diabetes	Patient survey @ 12 months (receipt of advice)	Clinician survey @ 12 months; QOF
**4.****Prescribe additional antihypertensive drugs** (*i.e.*, new drug or increased dosage) for patients with type 2 diabetes with uncomplicated hypertension whose blood pressure is at least 5 mmHg above 140/80 mmHg even following previous management	Practice computer prescribing data @ 12 months	Clinician survey @ 12 months; patient survey @ 12 months; QOF
**5.****Prescribe additional therapy for the management of glycaemic control (HbA1c)** in patients with type 2 diabetes whose HbA1c is higher than 58 mmol/mol (7.5%) despite maximum dosage on all oral hypoglycaemic drugs	Practice computer prescribing data @ 12 months	Clinician survey @ 12 months; patient survey @ 12 months; QOF
**6.** Personally ensuring that circulation and sensation in the feet of people with type 2 diabetes have been examined in the past 12 months, by **examining feet yourself and/or referring** them	Practice computer management data @ 12 months	Clinician survey @ 12 months; patient survey@ 12 months; QOF

*Note.* QOF = Quality and Outcomes Framework.

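### Foot examination is the only primary outcome whose pre-intervention rate is collected but left out of the primary model

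*Protocol article*

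**What the plan says.** The Main trial analysis section compares arms on each of the six behaviours with a multilevel regression model. Practice list size is a covariate throughout, and two further practice features may be added depending on bivariate correlations. On baseline performance the rule is specific: "For the two prescribing behaviours the rates at which patients received the behaviour prior to the intervention will also be included as covariates". No other behaviour is named.

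The section on prescribing behaviours and foot examination describes one data route for both. Prescribing and "foot examination are measured by extracting clinical and prescribing data from general practice computers using electronic queries". The window is stated once for the whole extract: "Data will be extracted for a 24-month period", that is, "12 months prior to and 12 months after the month within which the intervention is delivered". Among the items counted is "the number who have had: a foot check".

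Table 2 (Primary outcomes) gives the primary source for foot examination as "Practice computer management data @ 12 months". The three advising behaviours instead come from patients asked to "complete an anonymous postal questionnaire 12 months after the delivery of the intervention".

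**The concern.** Three primary outcomes come from practice records, and all three have a pre-intervention year in the extract. The model uses that year for two of them and ignores it for the third, without explanation.

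Two things follow. First, only 44 practices are randomised, stratified by list size alone, so the arms may well differ by chance in their existing foot-check rates. An unadjusted estimate carries that difference with it. Second, the foot outcome uses every registered patient with type 2 diabetes, so its precision is limited mainly by variation between practices. A practice's own earlier rate is the covariate most likely to explain that variation.

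The outcome also has little room to improve. Table 1 gives a rate of 91% in the earlier study, and the Discussion accepts that improvement may be harder to show here. The protocol counts the trial as positive if at least two of six behaviours change, so avoidable loss of power on one of them bears on the overall conclusion.

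**Working it through.** **1. Which primary outcomes have a baseline, and which use it**

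| Outcome | Primary source | Pre-intervention data | In the model |
|---|---|---|---|
| Nutrition advice, education, activity advice | Patient survey at 12 months | No | Not possible |
| Antihypertensive and glycaemic prescribing | Practice computer, 24 months | Yes | Yes |
| Foot examination | Practice computer, 24 months | Yes | **No** |

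**2. Reproducing the protocol's own power**

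Inputs from the Sample size section: 42.5% against 57.5%, 5% significance (two-sided assumed), 80% power, ICC 0.06, 20 patients per practice.

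- Design effect = 1 + (20 − 1) × 0.06 = 2.14.
- With the Fleiss continuity correction, 187 independent patients per arm are needed. 187 × 2.14 = 400, which is 20 practices of 20 patients.
- Power for 40 × 20, 44 × 20, 40 × 40 and 44 × 40 (practices × patients) comes to 80.1%, 84.0%, 89.4% and 92.1%. The protocol states 80%, 83.9%, 89% and 92%, so its figures reproduce.

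**3. Room for improvement on the foot outcome**

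At 91% only 100 − 91 = 9 points remain, so the planned 15-point effect cannot occur. With 22 practices per arm, ICC 0.06 and 200 patients per practice (assumed; the number is not given), the difference detectable with 80% power is 5.2 points unadjusted. That is 5.24/9 = 58% of the room left. The corresponding shares, at the earlier study's rates, are:

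- 23% for antihypertensive prescribing (40%, 20 patients per practice)
- 32% for glycaemic prescribing (59%, 20 patients)
- 25% for weight advice (51%, 40 patients)
- 37% for education (73%, 40 patients)

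**4. Effect of adding the baseline rate**

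Let r be the correlation between a practice's rates before and after delivery. Adjustment multiplies the variance of the practice-level comparison by about 1 − r². The equivalent number of practices is 44/(1 − r²). The protocol gives no value for r, so a range is shown.

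For 200 patients per practice the design effect is 1 + 199 × 0.06 = 12.94. The effective number per arm is 22 × 200/12.94 = 340, divided by (1 − r²) when adjusted. Power is from a two-sided two-proportion test at 5%, without continuity correction.

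| r (assumed) | Variance multiplier | Equivalent practices | Power, 91% to 95% | Power, 91% to 96% | Detectable difference (points) |
|---|---|---|---|---|---|
| 0 (as planned) | 1.00 | 44 | 53% | 75% | 5.2 |
| 0.3 | 0.91 | 48 | 57% | 79% | 5.0 |
| 0.5 | 0.75 | 59 | 66% | 86% | 4.6 |
| 0.7 | 0.51 | 86 | 82% | 96% | 3.9 |
| 0.8 | 0.36 | 122 | 93% | 99% | 3.4 |

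**5. Sensitivity, for 91% to 96%**

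- Patients per practice, ICC 0.06: unadjusted power is 73% at 100 patients and 77% at 300. At r = 0.5 it is 84% and 87%; at r = 0.7, 95% and 96%. Practice size matters little.
- ICC, 200 patients: at 0.03 unadjusted power is already 95%, so there is little left to gain. At 0.10 it is 55%, rising to 67% at r = 0.5 and 83% at r = 0.7.

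**The case against.** The strongest reply is that nothing here is invalid. Randomisation protects the unadjusted comparison, and the multilevel model already carries variation between practices into the confidence interval, so chance imbalance is allowed for. Collecting a pre-intervention year does not oblige the primary model to use it. The interrupted time series is also confined to the two prescribing behaviours, so the restriction may be deliberate. This much stands: the issue is efficiency and exposure to chance imbalance, not bias. But no reason for the restriction is given, and the grounds for adjusting prescribing apply equally to foot examination.

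The size of the gain is also open to challenge. The correlation is unknown, and at r = 0.3 power rises by only about 4 points. The ICC of 0.06 is one figure for all behaviours. The 95% and 96% targets are illustrative. The 91% is a patient-survey rate, whereas the trial outcome is taken from records and counts referral as well as examination. A recorded foot check may not match that definition exactly, which would lower r. All of this stands as a limit on the magnitude. None of it makes adjustment harmful: an imperfect baseline covariate is still valid and costs one practice-level degree of freedom, a price the protocol already accepts for prescribing.

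Finally, an analysis plan not shown here could settle the matter. However, the protocol is not silent. It names the behaviours to be adjusted, and a plan that followed it would repeat the omission.

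**Conclusion.** The concern holds. Foot examination is the only primary outcome with a collected pre-intervention rate that the primary model leaves out, and the protocol gives no reason. That rests on the text alone and is certain.

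The size of the loss is conditional. If r lies between 0.5 and 0.7, the variance of the effect estimate would fall by 25% to 49%. Power for 91% to 96% would rise from about 75% to between 86% and 96%, assuming ICC 0.06 and 200 patients per practice. The gain is small if r is 0.3 or less, or if the ICC is well below 0.06. The unadjusted analysis remains valid. Because this outcome appears to have the least room to improve, and the data are already in hand, the change should be made.

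**What to change.** Replace the sentence in Main trial analysis with one that covers every record-based outcome, for example: *For the three behaviours measured from practice records (antihypertensive prescribing, glycaemic prescribing and foot examination), the practice's rate in the 12 months before delivery will be a covariate.* Define the pre-intervention foot rate with the same record codes as the outcome, including referral if the extract holds it.

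Make the change before allocation is unblinded, so that it cannot appear to be driven by results. The cost is one sentence and one practice-level degree of freedom. No extra data, patients or practices are needed.

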## Methods

### Trial design

The study will be a cluster randomised controlled trial with the general practice as the unit of randomisation and analysis to protect against contamination and given the level at which the primary outcome will be measured. The intervention will be a multi-level intervention, delivered to teams but targeting individual-level variables (see CONSORT checklist in Additional file 1).

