### Control condition

The control group will be asked to complete baseline and follow-up process questionnaires, but will not receive any intervention session. The control group will not be able to access the intervention materials during the intervention period, but will be provided with access after the trial is complete.

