### Sample size

Practice-level: 44 practices. Individual-level: The study is powered to detect change in the primary outcomes (six different clinical behaviours) between intervention and control practices. For advising behaviours, the primary outcome measure will be patients’ reports of having received the specific behaviours. In this respect, a random sample of 100 patients with type 2 diabetes in each practice will be surveyed. For prescribing and examining behaviours, data will be extracted from the patient computer records of all patients with type 2 diabetes in each practice. Based on our previous study an intra-cluster correlation coefficient (ICC) of 0.06 is expected and to detect a 15% absolute improvement in any of our measures of behaviour (conservatively calculated as 42.5% to 57.5%) with 80% power and 5% significance, our primary and conservative sample size estimate is that we will need 20 patients from a total of 40 practices. As this sample size does not account for any potential loss to follow-up, we will recruit a further four practices (44 in total). Accordingly, two groups of 22 practices will provide us with 83.9% power to detect a 15% improvement in any behavioural outcome. Our previous study (iQuaD) has demonstrated that this level of recruitment at the patient level is achievable, as we received postal outcome data from a mean of 41 patients per practice (having invited 100) and extracted prescribing data on all patients with type 2 diabetes in the practice (from analysing these data we identified that about 20 patients per practice were eligible for the specified prescribing behaviours). Based on our previous study we anticipate a mean sample size of 40 patients per practice and will thus have greater power. Assuming 40 practices (two groups of 20), we would have 89% power to detect a difference of 15 percentage points (42.5% versus 57.5%) assuming a type 1 error rate of 5% and an ICC of 0.06; retaining all 44 practices would increase power to 92%.

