### Randomisation: type

Permuted-block randomisation, with practice list size as the blocking factor; 22 practices will be randomised to intervention, and 22 to control. The size of the permuted blocks will vary randomly.

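### The secondary 'as treated' analysis is open to confounding by practice uptake; a complier-average (CACE) analysis using allocation as the instrument suits this design better

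*Protocol article*

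**What the plan says.** The protocol article, under Main trial analysis, sets ITT as the main analysis: "practices randomised to receive the intervention will be compared with other practices". It then adds a secondary analysis, which it calls 'as treated', and says that this "analysis will take into account the uptake of the intervention in each practice". It does not define uptake, and it does not say how intervention practices that take up nothing are to be grouped.

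The same section lists the covariates. Practice list size is always included. A specialist diabetes clinic and onsite insulin prescription are to be considered. Pre-intervention rates are included for the two prescribing behaviours only.

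Under Control condition, control practices get no session, and "The control group will not be able to access the intervention materials during the intervention period". Under Randomisation: type, "22 practices will be randomised to intervention, and 22 to control".

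**The concern.** An 'as treated' contrast sorts practices by a choice made after randomisation. Practices that send their clinicians to sessions may differ from those that do not in ways that also affect the outcome. The protocol's Background gives some reason to expect this: in the preceding study, clinicians' own beliefs, such as intention and self-efficacy, predicted the target behaviours. The same beliefs could plausibly influence attendance, so uptake and outcome could share a cause.

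The planned covariates only partly deal with this. The three advising outcomes come from a patient survey done at 12 months alone, so they have no baseline rate to adjust for. Foot examination data are extracted for the preceding year, but the text does not name the prior rate as a covariate for that outcome.

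What is at stake is interpretation. This is the only stated estimate of the effect of receiving the intervention: the time series compares arms, the mediation models concern theoretical constructs, and the fidelity analysis is descriptive. If ITT were null, a favourable 'as treated' result could be misread as showing that the intervention works where it is taken up.

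**Working it through.** **The plan's own figures.** The article gives no figure for the 'as treated' analysis, so the check starts from Sample size: 42.5% against 57.5%, 5% significance, and "an intra-cluster correlation coefficient (ICC) of 0.06 is expected". With a continuity-corrected two-sided comparison of two proportions, 187 patients per arm are needed before allowing for clustering. With 20 patients per practice the design effect is 1 + 19 × 0.06 = 2.14, and 187 × 2.14/20 = 20.0 practices per arm, or 40 in total, as stated. Power comes to 80.1%, 84.0%, 89.4% and 92.1%, against the stated 80%, 83.9%, 89% and 92%. These inputs are sound and are used below.

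**Bias with no true effect.** Let u be the share of intervention practices that take up, and d the amount by which would-be takers outperform would-be non-takers anyway. Neither is in the documents; both are assumptions.

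- The treated group is 22u practices, all takers.
- If non-takers are pooled with controls, the untreated group is 22 + 22(1−u) = 22(2−u) practices.
- Would-be non-takers in it number 22(1−u) among controls and 22(1−u) in the intervention arm, a share of 2(1−u)/(2−u).
- Spurious difference = d × 2(1−u)/(2−u).
- If takers are compared with controls only, it is d(1−u).

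| u | pooled, d = 5 | pooled, d = 10 | controls only, d = 5 | controls only, d = 10 |
|---|---|---|---|---|
| 0.6 | 2.9 | 5.7 | 2.0 | 4.0 |
| 0.7 | 2.3 | 4.6 | 1.5 | 3.0 |
| 0.8 | 1.7 | 3.3 | 1.0 | 2.0 |
| 0.9 | 0.9 | 1.8 | 0.5 | 1.0 |
| 1.0 | 0 | 0 | 0 | 0 |

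Entries are percentage points, without covariate adjustment.

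**What d is plausible.** At a rate near 50%, an ICC of 0.06 implies a between-practice variance of 0.06 × 0.25 = 0.015, an SD of about 12 points. A d of 5 to 10 is under one SD. A d of 20 is about 1.6 SD, and uptake alone would then explain u(1−u)d²/0.015 of the between-practice variance: 0.16 × 0.04/0.015 = 43% at u = 0.8, and 0.24 × 0.04/0.015 = 64% at u = 0.6. That is too strong a link to plan on.

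**How CACE behaves.** With non-compliance possible in one arm only, CACE is the ITT difference divided by uptake. A simulation of 22 against 22 practices, 40 patients each, ICC 0.06 and 4,000 runs, at u = 0.8 and d = 10, gave:

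- true effect 0: 'as treated' about +3.3 points, CACE about 0 (−0.1);
- true effect 15: 'as treated' 18.3, ITT 12.0, CACE 14.8.

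The small shortfall is the usual bias of a ratio in a small sample, to first order −d(1−u)/(22u): −10 × 0.2/17.6 = −0.1 points here, and −10 × 0.4/13.2 = −0.3 at u = 0.6.

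**Its price.** The standard error was about 0.058 for CACE against 0.046 for 'as treated' at u = 0.8, and about 0.080 against 0.049 at u = 0.6. CACE adds no power, because its test is essentially the ITT test. At u = 0.8 the ITT difference is 0.8 × 15 = 12 points, with power of about 76% at 40 patients per practice.

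**The case against.** The strongest reply is that one sentence is being asked to carry too much. Taking uptake into account could mean a graded covariate, or takers against controls, and the detail may sit in an analysis plan that is not shown. This stands in part. A reader might infer that the protocol commits to pooling non-takers with controls, but the text does not fix that, and the pooled column applies only under that reading. The name 'as treated' is nevertheless stated, and its ordinary meaning is a non-randomised grouping. If something else is meant, the label needs correcting.

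The documents also give reasons to expect limited confounding. Practice size was the only organisational characteristic related to performance in the preceding study, and it is a covariate. Variation lay mainly between clinicians within practices. Practices agree in writing before attendance is arranged, so uptake may be high. For the two prescribing outcomes, prior rates are covariates, and nothing says that they would be dropped from the secondary analysis. All of this argues for a small bias; none of it rules bias out, least of all for the advising outcomes.

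Finally, CACE is not assumption-free. A reader might infer that it is unbiased whatever happens. It is not: it needs the exclusion restriction, meaning that allocation affects outcomes only through the uptake that is measured. Partial attendance, or use of the materials by clinicians who did not attend, would break that restriction under a badly chosen yes/no cut-off. This stands, and it shapes the fix.

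**Conclusion.** The point holds at modest size. Read in its usual sense, the 'as treated' analysis gives up the protection of randomisation and can show a difference of about 1 to 6 points when there is none. That range assumes u of 0.6 to 0.9, d of 5 to 10 points, non-takers pooled with controls, and no adjustment. It shrinks under the other grouping or with baseline adjustment. It vanishes if uptake is complete or unrelated to underlying performance.

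Two stronger conclusions are tempting and are not supported. One is that the trial's main finding is at risk: it is not, because ITT is the main analysis and nothing ties the criterion of change in at least two of six behaviours to the secondary analysis. The other is that the bias could approach the 15-point target: that needs a d of about 20 points with low uptake, which is implausible given the ICC.

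CACE suits this design because controls receive no session and no materials during the intervention period. There are then no takers in the control arm, and CACE estimates the effect in practices that took up the intervention.

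**What to change.** Replace the 'as treated' analysis with a CACE analysis, with these points settled before outcome data are seen:

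- **Uptake.** Define one practice-level measure. A yes/no measure should count any exposure to sessions or materials as uptake, so that non-uptake means no exposure. If a graded measure is preferred, such as the share of eligible clinicians attending, state the dose-response assumption that it needs.
- **Model.** Use randomised arm as the instrument, with the same covariates as the main analysis and allowance for clustering, for example practice-level two-stage least squares with list size as a covariate.
- **Reporting.** State the exclusion restriction, give the uptake rate, and report the CACE estimate and interval beside ITT for each behaviour, as a secondary estimate.

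The cost is a change of wording and one additional model per outcome, on uptake data that the planned analysis already requires. The downside is the wider interval shown above, which grows as uptake falls, and no gain in power over ITT.
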